### Follow-up

All the participants will be followed-up at three different points. At 3 and 12 months questionnaires will be sent to the participants’ home address, and returned by them in a pre-paid envelop. At 6 months the participants will undergo a functional examination and fill inn questionnaires (the same as at baseline) (Table 2 and 3). A receptionist makes the 6 months follow-up appointments, and a blinded physiotherapist, not knowing what treatment the patient has been given, will perform the examination (Fig. 1).

### Statistical analysis

All statistical analyses will be carried out using R version 3.2.5 (The R Foundation for Statistical Computing, www.r-project.org) and SPSS version 24 (SPSS Inc., Chicago, IL, USA) for windows. All tests will be two-sided, and *p* values less than 0.05 will be considered statistically significant.

Continuous variables will be reported as means ± SEM and categorical variables as percentages (%) ± SEM. The chi-square test will be used to test for group difference in percentages of categorical variables, while the two-sample *t*-test will be used to test for group difference in means of continuous variables. Analog non-parametric tests will be evaluated when strongly skewed distributions.

To estimate and compare the treatment effect of the two specific interventions at the four time points (baseline, 3, 6 and 12 months) we will use mixed effects models. All models will define treatment, time and treatment-by-time interaction as fixed effects, whereas a random intercept will be specified to account for correlated observations of the same individual (an exchangeable correlation structure assumed). Depending on the measurement level of the outcome under study, treatment effects will be presented as relative estimates (e.g., odds ratios, relative risk) or predicted mean differences with 95 % confidence intervals, corrected for multiple testing. Age, gender, body mass index, duration of pain and work status will be evaluated as additional adjustment variables.

We cannot exclude the possibility that missing outcome data may occur for a proportion of participants. The mixed effects model will produce unbiased effect estimates as the model uses a likelihood-based estimation procedure, provided the data are missing at random (MAR). Additionally, a multiple imputation method for missing data will be utilized if missing data occur in covariates as well.

Effect size (ES) for mean change will also be calculated by subtracting post-test scores (6 and 12 months) from baseline in the two groups, dividing it by the standard deviation (SD) of the change score.

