### Primary outcome

The primary outcome is pain, assessed by the *Numeric Pain Rating Scale (NPRS)* which assesses average pain intensity the last 2 weeks on a scale ranging from 0 (no pain) to 10 (worst). The scale has shown better reliability and responsiveness than the visual analogue scale [25].

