### Sample size calculation

The aim is to enroll a total of 128 participants in the study. Power calculations are based on a power of 80 % and a significance level of 5 % to detect a meaningful difference between the two intervention groups on the patient-reported primary outcome measure. Based on previous studies using the NPRS to measure pain intensity, a clinically significant difference can be estimated to be approximately 2 points with a standard deviation of 2. Power calculations based on these data indicate that a total of 16 participants in each group will be sufficient to detect a treatment difference after ended intervention. However, long term follow-up (12 months) and expectations of decrease in difference between the two intervention groups with 1 point, there is a need to increase each group to 64 participants.

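### The mixed model leaves the arms free to differ at baseline and does not adjust for baseline NPRS, so the 12-month comparison is less precise than the data allow

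*Protocol article*

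**What the plan says.** The Statistical analysis section of the protocol article analyses the outcomes by mixed effects models over four time points, baseline being one of them. The mean structure is fixed for every outcome: "All models will define treatment, time and treatment-by-time interaction as fixed effects". A random intercept supplies an exchangeable correlation. On covariates: "Age, gender, body mass index, duration of pain and work status will be evaluated as additional adjustment variables". Baseline NPRS is not in that list, and no equality of the arms at baseline is imposed. The effect is to be reported as a predicted mean difference (or a relative measure, depending on the outcome). The section does not say whether this is the difference at a visit or the difference in change from baseline.

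Under Randomization method, the allocation envelope is handed over only once baseline measurement is complete. Any baseline difference between the arms is therefore chance.

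The Sample size calculation works from 80% power at the 5% level. It says "a clinically significant difference can be estimated to be approximately 2 points with a standard deviation of 2" and then, for 12 months, "expectations of decrease in difference between the two intervention groups with 1 point, there is a need to increase each group to 64 participants". It uses no baseline correlation.

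**The concern.** Randomisation makes the true baseline difference zero, yet the model spends a parameter on estimating it. With complete data and no further covariates, a model with free treatment, time and interaction terms returns the observed mean of each arm at each visit. The 12-month effect is then one of two things: the raw difference at 12 months, which ignores baseline, or the raw difference in change, which subtracts all of it. Neither gives baseline its optimal weight.

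Precision is at stake. The confidence interval for the primary outcome is wider than it need be, and for one of the two contrasts power may fall below target. A chance imbalance in baseline pain also moves the estimate in either case: the follow-up difference is under-corrected for it and the change contrast over-corrected.

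**Working it through.** **Inputs.** From the Sample size calculation: difference 1 point at 12 months, SD 2, 64 per group, 80% power, 5% level. From Statistical analysis: two-sided tests. Assumed: rho, the correlation between baseline and 12-month NPRS, shown at 0.3, 0.5 and 0.7; SD 2 as the SD of scores at each visit (the article does not say which SD it is); complete data.

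**Step 1: the plan's own figures.** n per group = 2(1.96 + 0.84)² × SD² / difference².
- 2 points: 2 × 7.85 × 4 / 4 = 15.7, so 16, as stated.
- 1 point: 2 × 7.85 × 4 / 1 = 62.8, so 63. The exact t-test gives 63.8, so 64, as stated.

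The 64 per group is therefore the size for an unadjusted two-sample comparison of scores.

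**Step 2: effective SD of each 12-month contrast.**
- Follow-up difference: 2
- Difference in change: 2√(2(1 − rho))
- Baseline-adjusted: 2√(1 − rho²)

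The standard error is the effective SD × √(2/64). For example, at rho 0.3 the change contrast has SD 2√1.4 = 2.366 and SE 2.366 × 0.1768 = 0.418.

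**Step 3: results at 64 per arm, 1 point** (power from the two-sided t-test; the normal approximation is higher by less than one percentage point; n by normal approximation).

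| | rho 0.3 | rho 0.5 | rho 0.7 |
|---|---|---|---|
| SE, follow-up difference | 0.354 | 0.354 | 0.354 |
| SE, difference in change | 0.418 | 0.354 | 0.274 |
| SE, baseline-adjusted | 0.337 | 0.306 | 0.252 |
| Power, follow-up difference | 80.1% | 80.1% | 80.1% |
| Power, difference in change | 66.0% | 80.1% | 95.2% |
| Power, baseline-adjusted | 83.7% | 90.0% | 97.6% |
| n per arm for 80%, follow-up / change / adjusted | 63 / 88 / 58 | 63 / 63 / 48 | 63 / 38 / 33 |

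The standard errors agree with a generalised least squares calculation for four visits under exchangeable correlation, with the baseline means free and then constrained to be equal.

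**Step 4: variance relative to the adjusted analysis.**
- Follow-up difference: 1/(1 − rho²) = 1.10 / 1.33 / 1.96
- Difference in change: 2(1 − rho)/(1 − rho²) = 2/(1 + rho) = 1.54 / 1.33 / 1.18

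Both exceed 1 for every rho between 0 and 1.

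**Step 5: chance imbalance.** The SE of the baseline difference is 2 × √(2/64) = 0.354, so an imbalance above 0.5 point in either direction has probability of about 16%. At rho 0.5, a 0.5-point imbalance shifts the expected follow-up difference by 0.5 × 0.5 = 0.25 point. It shifts the change contrast by (0.5 − 1) × 0.5 = −0.25 point. Either is a quarter of the 1-point target.

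**The case against.** The stated model is conventional and valid. On the follow-up difference it delivers the 80% for which the trial was sized, so plan and sample size agree. That stands, and it limits the point to efficiency. A reader might infer that the analysis is biased or that 64 per group is wrong. The documents support neither: randomisation makes both contrasts unbiased, and the sample size reproduces.

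A reader might also infer that baseline NPRS is never used. That is too strong. The change contrast subtracts it, and when 12-month values are missing the likelihood draws on baseline and earlier visits. The identity with raw means holds only for complete data without covariates.

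Nor does the text show that the five listed covariates would be chosen after seeing results. They are named in advance. That they will be evaluated can mean supplementary adjusted analyses, and the details may sit in the full protocol or analysis plan. No criticism is made on that score.

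The gain depends on an assumed rho. Entry partly selects on pain (NPRS of at least 3 is one of four questionnaire criteria, of which two are needed), which may narrow the baseline spread and lower rho. At rho 0.3 the gain over the follow-up difference is only about 80% to 84%, and at rho 0.8 the change contrast has only 11% more variance than the adjusted one (2/1.8 = 1.11). These limits affect the size of the gain, not its direction.

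Finally, the two usual remedies are not identical under the stated exchangeable covariance, which forces one correlation on all visits. If the pooled value were 0.5 but the 12-month value 0.3 (both assumed), the constrained model's variance factor would be 1 + 0.25 − 2 × 0.5 × 0.3 = 0.95, against 1 − 0.09 = 0.91 with a visit-specific slope. The fix allows for this.

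The point is not one that the article simply leaves to another document, because the article fixes this mean structure for all models.

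**Conclusion.** The point holds as a loss of efficiency that can be removed at no cost. Whichever 12-month contrast is meant, the model as written is less precise than a baseline-adjusted one. Against the follow-up difference, adjustment would raise power from about 80% to about 84%, 90% or 98% at rho 0.3, 0.5 or 0.7. Against the change contrast the gain is from about 66%, 80% or 95%. The practical risk is that the contrast is unnamed: if change is reported and rho is below 0.5, power is under the planned 80%.

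These figures rest on an assumed rho, on SD 2 applying to scores at every visit, and on complete data. They apply to continuous outcomes, not to those reported as odds ratios or relative risks.

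**What to change.** Choose one of two models and state it in advance:
- model NPRS at 3, 6 and 12 months, with baseline NPRS by visit as a prespecified covariate; or
- keep all four visits but omit any treatment effect at baseline, and replace the random-intercept structure with a covariance that lets the correlation differ by visit.

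In either case, name the treatment difference at 12 months as the contrast. Do the same for the continuous secondary outcomes that are measured at baseline.

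The cost is a change of wording in the analysis section. Baseline NPRS is already collected, so no participants, visits or data are added, and the sample size can stay as it is.

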#### Questionnaires

Pain intensity ≥ 3 on the Numeric Pain Rating Scale (NPRS)Sumscore > 30 measured with Örebro Musculoskeletal Pain Questionnaire short form (ÖMPQ-SF)Neck Disability Index (NDI) > 14Shoulder Pain and Disability Inventory (SPADI) > 20

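### A random-intercept model over baseline, 3, 6 and 12 months understates the standard error of the 12-month change contrast if correlations fall with time

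*Protocol article*

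**What the plan says.** The Statistical analysis section specifies mixed effects models with fixed effects for treatment, time and their interaction. Baseline is one of the four modelled time points, so it is a response and not a covariate. Within-person dependence is handled by a random intercept alone, with "an exchangeable correlation structure assumed". This applies to all the models. No random slope, heterogeneous or unstructured covariance, robust standard error or check of the structure is mentioned.

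On missing outcomes the same section states: "The mixed effects model will produce unbiased effect estimates as the model uses a likelihood-based estimation procedure". It makes this conditional on data being missing at random (MAR), and on nothing else.

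Other parts of the article bear on whether the structure fits. Follow-up falls at 3, 6 and 12 months. Table 3 gives treatment as lasting 3–6 months. The Follow-up section has questionnaires posted at 3 and 12 months and completed at an examination visit at 6 months. The Sample size calculation gives one standard deviation for NPRS, 2 points, and no values by visit.

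**The concern.** A random intercept with a single residual variance forces two things: the same variance at all four visits, and the same correlation between baseline and 12 months as between 3 and 6 months. In repeated pain scores, measurements further apart are usually less alike. Here the spacing is uneven, and the last visit comes after treatment has ended for most participants.

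Because baseline is in the model as a response, the interaction term at 12 months is the between-arm difference in change from baseline. Its standard error depends directly on the baseline-to-12-month correlation. If that correlation is below the average the model imposes, the reported standard error is too small, the confidence interval too narrow and the type I error above 5 %. Twelve months is also the time point that sets the sample size.

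Second, when 12-month values are missing, the fitted covariance decides how earlier visits stand in for them. Likelihood validity under MAR therefore needs a correct covariance model as well.

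**Working it through.** **The plan's own figure.** The Sample size calculation uses "a power of 80 % and a significance level of 5" per cent, "approximately 2 points with a standard deviation of 2", and then "expectations of decrease in difference between the two intervention groups with 1 point", which leaves 1 point at 12 months. Tests are two-sided. By the normal approximation, n per group = 2 × (1.96 + 0.84)² × SD² / difference². This gives 16 for 2 points and 63 for 1 point. The t-test version for 1 point gives 63.8, that is 64, with 80.1 % power. The stated 16 and 64 reproduce. They rest on a plain comparison of means and are not affected by the present point.

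**Formulas.** Take complete data, n = 64 per arm and time as a categorical factor. The fitted arm-by-visit means are then the observed means. The random-intercept fit estimates a common variance v equal to the mean of the four visit variances, and a common covariance c equal to the mean of the six covariances.

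- Change contrast, model SE: √[(2/n) × 2(v − c)]
- Change contrast, true SE: √[(2/n) × (s₀² + s₁₂² − 2·cov₀,₁₂)]
- Plain 12-month difference, model SE: √[(2/n) × v]
- Plain 12-month difference, true SE: √[(2/n) × s₁₂²]
- Real two-sided alpha: 2 × [1 − Φ(1.96 × model SE / true SE)]

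**Assumed inputs (not in the article).** Correlations are 0.6 for adjacent visits, 0.5 for 0–6 and 3–12 months, and 0.4 for 0–12 months. Three patterns of visit SDs are set around the stated 2.

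**Worked case, SD 2 at every visit.** The mean correlation is (3 × 0.6 + 2 × 0.5 + 0.4)/6 = 0.533, so v = 4 and c = 2.133. Model SE = √(0.03125 × 2 × 1.867) = 0.342. True SE = √[0.03125 × (4 + 4 − 2 × 1.6)] = √0.15 = 0.387. The ratio is 0.88 and alpha is 8.4 %.

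| SDs at 0, 3, 6, 12 months | Change: model / true SE | Ratio | Alpha | Plain 12-month: model / true SE | Ratio | Alpha |
|---|---|---|---|---|---|---|
| 2, 2, 2, 2 | 0.342 / 0.387 | 0.88 | 8.4 % | 0.354 / 0.354 | 1.00 | 5.0 % |
| 1.6, 2.0, 2.1, 2.2 | 0.342 / 0.379 | 0.90 | 7.7 % | 0.351 / 0.389 | 0.90 | 7.7 % |
| 2.2, 2.1, 2.0, 1.8 | 0.348 / 0.392 | 0.89 | 8.2 % | 0.359 / 0.318 | 1.13 | 2.7 % |

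**Sensitivity.** Moving the two-step correlations between 0.45 and 0.55 in these three patterns gives change-contrast ratios of 0.87–0.92 and alpha of 7.2–9.0 %. Steeper decay does more harm: with SD 2 throughout and a correlation of 0.7 per visit step (0.7, 0.49, 0.34), the SEs are 0.328 and 0.405, ratio 0.81, alpha about 11 %. Without decay the error disappears or reverses: a constant correlation of 0.5 gives a ratio of 1.00 with equal SDs, and 1.06 (alpha 3.8 %) with SDs of 1.5, 2, 2, 2.

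**Missing data.** A large simulation used 200,000 per arm, no true effect, a correlation of 0.7 per step and 22–29 % dropout by 12 months depending on the last observed score. With equal SDs, bias in the 12-month difference under the random-intercept fit was below 0.02 point, about the size of the simulation error. With SDs rising from 1.8 to 2.2 and dropout that depended on the score differently in the two arms, it reached about 0.05 point, against a 1-point target.

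**The case against.** A random intercept is a conventional, openly declared choice, and a separate analysis plan may add covariance checks, robust standard errors or a degrees-of-freedom method. That is fair for details the article leaves open. But this structure is stated, and for all models, so it can be judged as it stands.

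The stronger objection is that the effect depends on the contrast. The article promises predicted mean differences, which may mean the plain difference at 12 months. With complete data and equal variances, the standard error of that difference is exactly right whatever the correlations. This stands. A reader might infer that any 12-month standard error from this model is too small; the document does not support that. The plain difference has too small an SE only if the 12-month variance is above the visit average, and too large an SE if it is below.

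Nor does eligibility settle the direction. A pain score of at least 3 looks like a restriction on the baseline spread, but it is one of four questionnaire criteria of which any two suffice. Participants with lower scores can enter, and there is no hard truncation.

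A reader might also infer that the MAR statement fails in a way that matters. It is incomplete in principle, but the bias found was small.

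**Conclusion.** The point holds for the treatment-by-time contrast, on the condition that correlations fall with time. Under moderate decay, its model-based standard error at 12 months is about 10–12 % too small and the real two-sided type I error about 8 %, with 7–9 % under nearby assumptions. This holds whether the visit variances rise, stay level or fall in the patterns tried. For the plain 12-month difference the direction is unknown, because the article gives no SDs by visit. The incomplete condition for unbiasedness under MAR is a minor, secondary matter.

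All correlations, visit-specific SDs and dropout rates here are assumptions; only the SD of 2 and the 64 per group come from the article. The sample size is untouched. This is a worthwhile and inexpensive improvement to the specification, not a flaw that undermines the trial.

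**What to change.** For the continuous outcomes, including NPRS, replace the random intercept with an unstructured covariance matrix over the four visits: 4 variances and 6 covariances, 10 parameters in all. Fit by REML with Kenward-Roger or Satterthwaite degrees of freedom. Name a heterogeneous structure as the fallback if the model does not converge. Extend the missing-data sentence to say that unbiasedness requires MAR and a correctly specified model, including the covariance.

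Robust standard errors would be a partial alternative: they repair the standard errors but not the role of the covariance in handling missing values.

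The cost is one line of model specification, 8 more variance parameters than the present 2, and slightly fewer degrees of freedom, which 128 participants should support.

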## Discussion

We have presented the protocol for a pragmatic RCT, investigating the effectiveness of Norwegian Psychomotor Physiotherapy (NPMP) for patients with neck and shoulder pan and/or widespread pain, when compared to cognitive pain education combined with active physiotherapy (COPE-PT). The primary outcome of this study will be pain, assessed by the *Numeric Pain Rating Scale (NPRS).* Wand et al. [55] argue that there is a need of both self-reported and physically tested functioning to better grasp aspects of disability among patients with musculoskeletal pain. Accordingly, the secondary outcomes include both self- reported and tested function.

When choosing outcome measures, it is crucial to ensure congruence between the content of the treatment and the outcome. The NPMP is based on the understanding of the body as an integrated physical and psychological phenomenon and thus bodily change in the treatment might be followed by an emotional change. In order to grasp different aspects of the treatment, several secondary outcome measures of both physical function and mental health are necessary and therefore included in this study. In addition, all measurements are well-known and shown to be valid and reliable, as well as they measure different aspects of functioning according to the International Classification of Functioning and Health [56].

Several potential confounding factors may have an impact on both the primary and secondary outcomes. These may include factors as participant age, duration of pain, and psychological factors. Our randomized design is expected to distribute these variables equally between the two intervention groups. The blinding of the physiotherapist performing and collecting the follow-up data will also enhance the validity of the study. The performance of power analysis and sample size estimation is also an aspect to improve the precision to provide reliable answers to the primary outcome measure.

However, compliance with intervention might be a possible threat to the validity. This is a challenge because different physiotherapists (*n* = 10) are involved in the two treatment approaches. In addition NPMP is individually tailored which further increases the complexity, since the treatment will not only vary between individuals but also between physiotherapists. In order to ensure compliance, all the physiotherapists in both treatment approaches will be regularly followed by separate meetings for therapists in each of the two interventions, discussing how they implement and internalize the treatment during the study period. In addition, as the treatments are pragmatic the therapists will register more details regarding content and number of treatment given. A strength, however, is that the treatment will occur in natural settings, hence, its practicality and feasibility may be high.

In summary, the findings of the present study may give an important contribution to our knowledge of the outcome of NPMP, on patients with long-lasting widespread musculoskeletal pain and/or pain located to the neck and shoulder region.

## Abbreviations

NPMP, norwegian psychomotor physiotherapy; COPE-PT, cognitive pain education and active physiotherapy; RCT, randomized controlled trial; NPRS, numeric pain rating scale; ÖMPQ-SF, Örebro musculoskeletal pain questionnaire short form; NDI, neck disability index; SPADI, shoulder pain and disability inventory; GPE-Flexibility, global physiotherapy examination – flexibility; SHC, subjective health complaints inventory; HSCL-25, Hopkins symptoms checklist; TSK, tampa scale of kinesiophobia; SF-12, short form-12; BIS, bergen insomnia scale; CSQ-8, client satisfaction questionnaire; BPS, back performance scale; ACR, The American College of Rheumatology; ICC, intraclass correlation coefficients; SEM, standard error of measurement; ES, effect size; SD, standard deviation
